### Study Setting and Procedures

All participants, regardless of intervention assignment, complete the same study measurement protocol. The study setting includes onsite visits at the Penn State Clinical Research Center (University Park campus) and at-home participation. Interested and eligible women complete a preintervention assessment at the Penn State Clinical Research Center after the study is described and written consent is obtained. A study clinician assesses height, weight, blood pressure, and conducts a physical exam to identify health symptoms that may preclude study participation [29]. Women complete self-reported measures of their healthy eating/physical activity behaviors, knowledge, planned and self-regulatory behaviors, motivational determinants, demographics, and dietary intake using onsite paper and pencil and Web-based data capture software (Research Electronic Data Capture) [51].

Women then complete an air displacement plethysmography body composition assessment following a standardized protocol that takes approximately 30 min. Participants complete these same measures again at the postassessment at approximately 36 weeks gestation. In addition, during the course of the study all women are given a Wi-Fi scale for wireless uploading of daily weight, food scale to monitor daily intake, and log to record food and beverages (and amounts) consumed, and 2 monitors (wrist-worn activity monitor worn daily; waist-worn accelerometer worn in 2-week cycles) to track physical activity. Participants are asked to use these mHealth devices continuously over the course of the entire study. Women track dietary intake on 2 weekdays and 1 weekend using a mobile phone app. Measures are obtained at baseline, during the intervention (daily, weekly, and monthly), and postintervention. All participants are compensated up to US $420 in check or gift card for the pre and post, weekly, and monthly assessments over the study period. In addition, the intervention participants get to keep their Wi-Fi weight and food scales at the end of the study (control participants return them), and they receive a US $20 check if they attend 90% (25/28) or more of the intervention sessions.

### Decision Rules and Adapting the Intervention Dosage

A set of decision rules were developed to evaluate GWG that are based on the Institute of Medicine GWG guidelines (ie, overweight=15-25 pounds; obese=11-20 pounds) [1], our own research [36,37,50], and clinical insight that inform when and how to adapt the components. A computerized applet is used to plot women’s weight against individual weight gain trajectories with lower and upper bounds for the GWG guidelines [52,53]; GWG is evaluated weekly and the values are compared with average weekly weight ranges for overweight (eg, 0.5-0.7 pounds) and obese (eg, 0.4-0.6 pounds) women [1]; these weekly weights are then evaluated in 3-4 week cycles to determine if and when the intervention dosage should be adapted (see Multimedia Appendix 2). The rationale for adapting the dosages is based on each woman’s self-regulatory abilities to manage GWG. For example, if the woman is within her GWG goal (ie, weekly weight gain ranges according to the Institute of Medicine guidelines) [1], she will continue to receive the same level of the intervention for the next cycle as she is adequately self-regulating her weight with the amount of intervention dosage that she’s receiving. However, if she is exceeding her GWG goal, the intervention is adapted (ie, dosage is stepped up). That is, she continues to receive the baseline intervention, but then she receives additional active learning components (eg, step-up 1 with cooking and grocery store demonstrations; onsite exercise session led by an instructor) to help better self-regulate her weight. If she exceeds her GWG goal at the next evaluation cycle, the intervention will be adapted again (ie, baseline + step-up 1 + step-up 2) with other active learning components (eg, portion size and containers; second onsite exercise session with instructor) added to provide more intensive intervention assistance and supportive control to better manage GWG. This evaluation process continues over the course of her pregnancy until the end of the intervention (ie, around 36 weeks gestation) and/or a maximum of 5 possible dosage increases (see Multimedia Appendix 3). The sequencing of the adaptive dosages was determined during pilot testing by examining combinations of active learning strategies with good user acceptability, and we identified the maximum number of dosage increases that resulted in “too much intervention burden” and led to participant dropout (ie, more than 5 adaptations) [50]. If a participant is under her GWG goal [1] and/or any safety concerns emerge (eg, complication such as anemia, fetal issue), we consult with the study obstetrician who makes recommendations on if and/or how intervention dosage changes should be made.

### Outcome Measures

The measurement protocol is presented above in Table 1. The primary outcome measure is GWG. Weight and GWG are assessed pre- and postintervention at the Penn State Clinical Research Center using standardized procedures (eg, measured in duplicate to nearest kilogram using a high-precision stand-on adult scale; wearing undergarments and gown) and daily at home using the Wi-Fi wireless scale. Secondary outcomes include adiposity (body composition), healthy eating behaviors, physical activity behaviors, knowledge, motivational determinants, self-regulation, psychological well-being, sleep, serum blood for macronutrients, stress (cortisol), metabolism, and fetal growth.

### Data Collection

Data on the primary and secondary outcome variables above are collected in addition to participant sociodemographic characteristics (eg, age, BMI status) to understand the influence of potential moderators on the primary and secondary outcome variables. Standardized procedures were developed for data collection, recording of errors, and a comprehensive data quality assurance program to ensure complete, accurate, and valid data while limiting variability in data recording. Study data are managed using a secure Web app that provides user-friendly Web-based case reports, real-time data entry validation audit trails, and a deidentified data export mechanism to commonly used statistical packages.

### Data Analysis

To establish initial validation of the intervention, contrasts constructed from linear mixed-effects models [54] will be used to assess differences between the intervention and control groups with respect to changes in continuous outcomes over time (from pre- to postintervention): changes in primary (GWG, energy intake, physical activity, planned/self-regulatory behaviors) and secondary outcomes (serum blood biomarkers, adiposity, knowledge). Linear mixed-effects models are an extension of ordinary regression models that account for within-subject variability inherent in longitudinal studies. Generalized estimating equations [55] with a logit link will be used to assess differences between the intervention and control groups with respect to dichotomous outcomes over time. If deemed necessary, confounding variables (eg, prepregnancy weight, age, obstetric complications) will be included as covariates. With respect to the participants meeting individual GWG goals based on prepregnancy BMI status [1], we will look at each woman and determine whether she met her GWG goal. We will code participants as “0” for GWG within goal, +1 for GWG over goal, and −1 for GWG under goal. A chi-square test will be used to assess differences between the intervention and control groups on this 3-level ordinal variable (ie, −1,0,1) assessing individual GWG goals. All hypothesis tests will be 2-sided, and analyses will be performed using SAS software version 9.4 (SAS Institute Inc., Cary, NC) or R software (R Foundation for Statistical Computing, Vienna, Austria).

Modeling development and simulation are done in Matlab with SIMULINK (The MathWorks, Inc., Natick, MA). Functional data analysis modeling for time-varying modeling will rely on SAS. Weight predictions based on a first-principles energy balance model can be performed using measurements of a participant’s energy expenditure (physical activity and resting metabolic rate) and energy intake. Alternatively, energy intake can be estimated from the energy balance model using the measured weight gain and physical activity, which can then be compared with self-reported data [56,57]; this information can be used by dieticians to provide informative health guidance. Intensive measurements of the Theory of Planned Behavior constructs are used to build participant-based dynamical models using semiphysical model identification techniques. The integration of these behavioral models with energy balance models can be used to evaluate and implement decision policies based on control systems engineering for an intensively adaptive intervention, specifically Hybrid Model Predictive Control [37,58].

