### Participants and Sample Size

The target sample for this intervention is 30 pregnant women with overweight and obesity (BMI range 25-45 kg/m^2^; >40 kg/m^2^ with physician consultation); singleton pregnancy >8 weeks gestation; English-speaking; residing in or near Centre County, Pennsylvania; and with physician consent to participate. On the basis of our past research [27,28], this group compromises >85% of live births in Central Pennsylvania. Exclusion criteria are multiple gestation, diabetes at study entry, not overweight or obese, severe allergies or dietary restrictions, contraindications to prenatal physical activity [29], and not residing in area for duration of the study. The primary outcome of our study is GWG. Julious [30] effectively argues a sample size of 12 per group is adequate to assess feasibility and obtain sufficient precision of the mean and variance to perform a formal sample size and power calculation for a future larger randomized control trial with GWG as the primary outcome. With 24 participants (12 per group), we will have 80% statistical power to detect a standardized effect size (difference between 2 group means divided by SD) for GWG of 1.2 using a 2-sided test with significance level of *P*=.05. Factoring in participant dropout (conservative estimate of 25% based on our pilot work [31,32] and past research [5]), we will recruit 30 participants (15 intervention, 15 control).

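### The planned pre-to-post change contrasts do not commit to using each outcome's preintervention value, which gives up precision for moderately correlated outcomes other than GWG

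*Protocol article*

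**What the plan says.** The Data Analysis section describes its tests of continuous outcomes as follows: "contrasts constructed from linear mixed-effects models [54] will be used". The aim it gives for these models is "to assess differences between the intervention and control groups with respect to changes in continuous outcomes over time (from pre- to postintervention"). It applies this to GWG, energy intake, physical activity and planned or self-regulatory behaviors, all of which it calls primary, and to serum biomarkers, adiposity and knowledge as secondary outcomes.

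Adjustment is conditional: "If deemed necessary, confounding variables (eg, prepregnancy weight, age, obstetric complications) will be included as covariates". The preintervention value of the outcome is not among the examples. The section does not say whether that value enters the mixed model as a response or as a covariate, or whether the arms' preintervention means are free or held equal.

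The baseline data exist. Study Setting and Procedures says of the preintervention visit: "Women complete self-reported measures of their healthy eating/physical activity behaviors, knowledge, planned and self-regulatory behaviors, motivational determinants, demographics, and dietary intake". Body composition is measured at the same visit. Then: "Participants complete these same measures again at the postassessment at approximately 36 weeks gestation". Table 1 marks preintervention measurement for accelerometry, the eating questionnaire, the motivational determinants, the self-regulation scales, serum and body composition. The Results section reports baseline data for all participants.

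On the outcome and its power, Outcome Measures says "The primary outcome measure is GWG" and, on how it is measured, "Weight and GWG are assessed pre- and postintervention at the Penn State Clinical Research Center using standardized procedures". Participants and Sample Size says "With 24 participants (12 per group), we will have 80% statistical power to detect a standardized effect size" of 1.2 for GWG, two-sided at 0.05.

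**The concern.** With two occasions, complete data and a free preintervention mean in each arm, a mixed-model contrast of change equals a comparison of change scores. It subtracts the baseline in full, with a slope fixed at 1, whatever the true relation between the pre and post values. Randomization makes the expected baseline means equal. A model that uses this fact, by a common preintervention mean or by regression on the preintervention value, removes only as much of the baseline as is predictive.

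The listed covariates do not fill the gap. Prepregnancy weight is a near stand-in for baseline weight. Neither it nor age stands in for baseline activity, self-regulation, serum or adiposity.

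What is at stake is interval width. The analysis is meant to give an initial validation of the intervention on about 24 women, and no further recruitment is planned that would recover lost precision. An adjustment made only when judged necessary also leaves the choice of model open after the data are in.

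**Working it through.** **The plan's own figure.** Inputs from Participants and Sample Size: 12 per group, standardized difference 1.2, two-sided 0.05. The noncentrality is 1.2 × √(12/2) = 2.94 on 22 degrees of freedom. The noncentral t gives 80.2% power, so the stated 80% reproduces as a two-sample t-test without a covariate.

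**Direction of the effect.** Let s0 and s1 be the pre and post SDs and ρ the pre-post correlation within arm. Per woman, in large samples:

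- change score: s0² + s1² − 2ρ·s0·s1
- conditional on baseline: s1²(1 − ρ²)
- difference: (s0 − ρ·s1)², which is never negative

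So in large samples conditioning is never worse, whatever the two variances are.

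**Size, with equal variances (an assumption).** The ratio of conditional to change-score variance is (1 − ρ²)/[2(1 − ρ)] = (1 + ρ)/2.

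**Small-sample cost.** Estimating the baseline slope with 24 women multiplies the conditional variance by about 1 + 1/20 = 1.05, because the within-group baseline sum of squares has 22 degrees of freedom and the mean of 1/χ² on 22 is 1/20. The net ratio is therefore 1.05 × (1 + ρ)/2. The documents give no ρ, so the range is shown.

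| Assumed ρ | (1 + ρ)/2 | × 1.05 | Net change in variance |
|---|---|---|---|
| 0.3 | 0.650 | 0.6825 | 32% less |
| 0.5 | 0.750 | 0.7875 | 21% less |
| 0.7 | 0.850 | 0.8925 | 11% less |
| 0.8 | 0.900 | 0.945 | 5.5% less |
| 0.9 | 0.950 | 0.9975 | about 0 |
| 0.95 | 0.975 | 1.0237 | 2.4% more |

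At ρ = 0.5 the interval width is multiplied by √0.7875 = 0.887, about 11% narrower. The break-even is ρ = 2/1.05 − 1 ≈ 0.90.

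**Check by simulation** (20,000 trials, 12 per arm). At ρ = 0.5 the variance of the estimated effect was 0.1667 for change scores and 0.1312 with the baseline covariate, a ratio of 0.788 against 0.7875 by formula. At ρ = 0.95 the ratio was 1.019 against 1.024.

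**GWG.** GWG is itself a change in weight, and its baseline is body weight. Weights of the same woman at entry and at about 36 weeks are plausibly correlated at 0.9 to 0.95 (an assumption). Dividing 1.2 by the square root of the net ratio, on 21 degrees of freedom, gives 80.1% power at 0.9 and 79.1% at 0.95, against 80.2% for the change score. There is nothing to gain.

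**The case against.** Four points on the other side have weight.

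1. **The model may already do this.** The article names only contrasts from mixed models. A model with a common preintervention mean fits that wording, and the detail may sit in a fuller document that is not shown. This stands. A reader might infer that the plan rules out conditioning on baseline; the text does not say so. What can be said is that it describes a change contrast, does not commit to using the baseline, and names other covariates as optional.

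2. **Many outcomes have more than two occasions.** Table 1 has accelerometry, the eating questionnaire and the motivational determinants monthly as well, and the main self-regulation scales biweekly. With a time trend, a structured covariance or missing data, the contrast need not equal a simple change score, and the ratio above is then only a guide. Serum, taken only pre and post, and the pre-to-post contrast for body composition fit the two-occasion form directly.

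3. **The sizes rest on an assumed correlation.** This stands. A reader might infer that a quarter of the variance is wasted on every outcome. That is the large-sample value at ρ = 0.5; with 24 women it is 21%, and neither 0.5 nor any other correlation is in the documents. A reader might also infer that the trial's 80% power would rise to about 88%. That figure comes from applying the 1.2 effect at ρ = 0.5, but 1.2 is stated for GWG only, where 0.5 is implausible. No effect size is given for the outcomes that would benefit.

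4. **Nothing is biased.** Correct. A reader might infer that chance baseline differences make the change contrast wrong. Conditional on a given imbalance the estimate can be shifted, and with 12 per arm sizeable imbalances do occur, but over randomizations it is unbiased and the test is valid.

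None of this removes the expected gain for moderately correlated outcomes, some of which the Data Analysis section itself calls primary.

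**Conclusion.** The point holds as one of precision. The stated analysis compares changes and leaves the use of the preintervention values uncommitted, although they are in hand. Unless the mixed model already constrains the preintervention means, the loss for a given outcome depends on its correlation: conditioning would save about 32% of the variance at 0.3, 21% at 0.5, 11% at 0.7 and 5.5% at 0.8. This assumes 12 women per arm, two occasions and equal pre and post variances. Physical activity, planned and self-regulatory behaviors, serum and adiposity are the outcomes likely to benefit. For GWG, at an assumed 0.9 to 0.95, the effect runs from nil to a loss of about 2%, and the plan's power statement is unaffected. It is a cheap improvement to a valid analysis.

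**What to change.** In Data Analysis, add a sentence such as:

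> For each continuous outcome other than GWG that is measured preintervention, the mixed model will constrain the two arms to a common preintervention mean (or include the preintervention value as a fixed covariate), and the treatment effect will be the between-arm difference at postintervention.

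For GWG this is optional, and no power gain should be claimed for it. If the intended model already constrains the preintervention means, a sentence saying so settles the matter.

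The cost is wording and one model statement, with no new data. It uses at most one degree of freedom; the roughly 5% price of estimating the slope is already counted in the savings above and outweighs the benefit only when the correlation exceeds about 0.90.

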### Strengths and Limitations

There are several positive features of this study. This study has strong public health relevance and clinical significance for the future management of GWG. We have also incorporated several innovative aspects into the study, including the use of (1) novel decision rules to choose when and how to adapt the intervention, (2) mHealth tools for self-monitoring of behaviors and real-time data collection to provide feedback to the participants, and (3) a unique computerized applet to generate individualized weight gain trajectories for comparing actual weight to the Institute of Medicine guidelines. In addition, customized eating and physical activity plans developed for this study aid in reducing participant barriers to engaging in healthy behaviors during pregnancy. Moreover, the intensive longitudinal data collection protocol allows for a myriad of systems approaches in support of implementing and evaluating intensively adaptive interventions [25,56-58]. Intensive data collection enables the application of system identification and state estimation approaches from engineering that, in turn, build comprehensive dynamical models for GWG used in adaptive intervention optimization. These methods can be used to estimate and correct energy intake over time, despite some missing data.

There are also some limitations of this research. The small sample size, although adequate for examination of the primary outcome (GWG), precludes the ability to make assumptions at a population level. Moreover, the target population is a homogenous sample of women from largely rural and suburban areas in Central Pennsylvania, thus limiting the extension of the study findings to more culturally diverse and urban populations of pregnant women with overweight and obesity. We do plan to understand the application of Healthy Mom Zone to a more diverse sample of pregnant women in the future, including those who are normal weight, more culturally diverse, and reside in varied communities across the United States.

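### The Data Analysis section labels three behavioral domains as primary beside GWG, while the sample size, outcome and limitations sections make GWG the only primary outcome

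*Protocol article*

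**What the plan says.** Three sections of the protocol article name a single primary outcome:

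- Participants and Sample Size: "The primary outcome of our study is GWG". The power statement there is tied to that outcome: "With 24 participants (12 per group), we will have 80% statistical power to detect a standardized effect size" of 1.2 for GWG, "using a 2-sided test with significance level of *P*=.05".
- Outcome Measures: "The primary outcome measure is GWG". The same paragraph goes on: "Secondary outcomes include adiposity (body composition), healthy eating behaviors, physical activity behaviors, knowledge, motivational determinants, self-regulation", followed by further secondary measures.
- Strengths and Limitations: "The small sample size, although adequate for examination of the primary outcome (GWG), precludes the ability to make assumptions at a population level".

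The Data Analysis section sets out mixed-model contrasts between the groups for "changes in primary (GWG, energy intake, physical activity, planned/self-regulatory behaviors) and secondary outcomes (serum blood biomarkers, adiposity, knowledge". That makes four primary domains and a separate, shorter secondary list. On testing it adds: "All hypothesis tests will be 2-sided, and analyses will be performed using SAS software version 9.4" or R. The article does not say how the four domains rank among themselves or what result would count as success.

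**The concern.** Physical activity and self-regulation carry opposite labels in two sections of the same Methods. Energy intake is less clear-cut. Outcome Measures does not name it, and the nearest entry there, healthy eating behaviors, is secondary.

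The label decides how a result is reported and read. With two hierarchies in print, a group difference in physical activity could be presented as a primary finding, or a null one as secondary, and each choice would have support in the text. The Results part of the abstract says that most participants had already completed and that analysis was still under way, so the choice could be made with data in hand.

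The label also bears on the sample size. The stated power is for one outcome tested at one two-sided 0.05 level. It fits a single primary outcome. It does not by itself cover four primary outcomes of equal standing.

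**Working it through.** **1. The labels side by side**

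| Domain | Sample Size; Limitations | Outcome Measures | Data Analysis |
|---|---|---|---|
| GWG | primary | primary | primary |
| Physical activity | not listed | secondary | primary |
| Self-regulation | not listed | secondary | primary (within planned/self-regulatory behaviors) |
| Energy intake | not listed | not named; healthy eating behaviors is secondary | primary |

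The conflict is direct for physical activity and self-regulation, and indirect for energy intake.

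**2. Reproducing the stated power**

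Inputs from Participants and Sample Size: 12 per group, standardized difference d = 1.2, two-sided 0.05.

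Two-sample t test with the noncentral t distribution:

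- degrees of freedom = 2 × 12 − 2 = 22
- noncentrality = d × √(n/2) = 1.2 × √6 = 2.94
- critical value at two-sided 0.05 = 2.074
- power = 80.2%

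The plan's 80% is therefore reproduced for one GWG test at 0.05.

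**3. Family-wise error with four primary domains**

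Assumptions, none of them stated in the article: each domain is tested once at 0.05, there is no adjustment, and any one significant result may be called a primary finding.

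- Independent tests: 1 − 0.95⁴ = 1 − 0.8145 = 18.5%.
- Correlated tests, by simulation of four equally correlated normal test statistics, each with critical value 1.96 and one million draws per setting:

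| Assumed correlation | Family-wise error |
|---|---|
| 0 | 18.5% |
| 0.3 | about 17% |
| 0.5 | about 16% |
| 0.8 | about 11% |

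The documents give no correlations, so these values only show the range.

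**4. What controlling the error would do to GWG power**

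- *Bonferroni over four:* 0.05 / 4 = 0.0125 per test. With 22 degrees of freedom the critical value is 2.720, and power at d = 1.2 falls to 59%. The difference detectable with 80% power rises from about 1.20 to 1.47. Restoring 80% at d = 1.2 would take 18 per group.
- *Fixed sequence with GWG first at 0.05:* the GWG test is unchanged, so its power stays at 80.2%. The other domains would be tested only after a significant GWG result.
- *GWG as the single primary outcome:* the GWG test again keeps its 0.05 level and 80.2% power.

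**The case against.** Much of the case on the other side stands.

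- **Editorial slip.** The Objectives section lists nearly the same domains as targets of the initial validation without calling them primary. Data Analysis may simply have repeated that list and mislabelled it. This is plausible, since the hierarchy is stated consistently in three other places. But Data Analysis also gives its own secondary list, so a reader cannot tell a slip from a decision.
- **Feasibility-sized study.** The group size is justified chiefly by feasibility and by precision for planning a later trial, and efficacy is left to that trial. This lowers the stakes. It does not remove them, because the article also makes a formal power claim and plans two-sided group comparisons.
- **No success rule and no shown adjustment.** A reader might infer that the plan lets success be claimed on any of several unadjusted tests. The documents do not support that. No success criterion is written down, and the absence of an adjustment rests on the silence of a condensed article. Handling of multiplicity may sit in a fuller document, so its absence here is no finding.
- **Power under error control.** A reader might also infer that any error control would void the 80% power. That is not so. It is lost under a rule that splits alpha, such as Bonferroni, but not when GWG is tested first at 0.05.
- **Size of the error rate.** Weight, intake and activity are linked in the study's own energy balance model, so independence gives the high end of the range for four tests. Larger rates could be produced by counting individual scales in Table 1, but the article does not say which scales would be tested as primary, so such counts would be guesswork.

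None of this reconciles the two sections. An analysis plan that is not shown cannot make Outcome Measures and Data Analysis agree.

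**Conclusion.** The contradiction holds as the text is written, and it should be fixed. GWG is the single primary outcome in three sections and one of four primary domains in Data Analysis. Physical activity and self-regulation are labelled both ways. This conclusion needs no assumption.

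The numerical consequence is conditional. If any one of four domains tested at 0.05 could count as a primary finding, the family-wise error would lie between about 11% and 18.5% for assumed correlations from 0.8 down to 0. That is roughly two to four times the nominal 5%. The fall in GWG power to 59% applies only if alpha is split by Bonferroni.

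The matter is not more serious than this. The weight of the text favors GWG alone, the stated power reproduces for GWG, and the trial is presented as a feasibility-sized first validation.

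**What to change.** In Data Analysis, leave GWG as the only outcome described as primary. Move energy intake, physical activity and planned/self-regulatory behaviors to the secondary list. Report those three domains with estimates and confidence intervals, and make no confirmatory claim on them. The section then agrees with Participants and Sample Size, Outcome Measures, and Strengths and Limitations, and the 80% power statement stands as written.

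The cost is one edited sentence. No data collection, model or sample size changes. The downside is that no result on the behavioral outcomes can be presented as a primary finding.
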